#### 2.5.1. Activity Metrics and Educational Content

The activity metrics and data to be collected through the mobile app will be defined by the results of the group concept mapping conducted in the initial phases of the project. In line with the general objectives of the E-Walk project, and to comprehensively monitor both physical and educational engagement, the collected data will be organized into three main categories:Anthropometric Data: related to children’s growth and body composition, defined according to health promotion priorities.Physical Activity Parameters: measuring level, type, and intensity of activity, determined by technical feasibility and user preferences, and PAQ-C.Activity Enjoyment and User Feedback: To evaluate participants’ perceptions regarding the proposed activities, including their motivational impact, enjoyment, and usability. The tools and methods used to collect this type of feedback will be tailored according to the results of the concept mapping process, the app’s development, and the preferences identified among children and other stakeholders.

Educational content will also be integrated in the app to stimulate cognitive engagement. Its structure and topics will be developed based on concept mapping results, ensuring alignment with user needs and supporting the overall project objectives.

#### 2.5.2. Planned Mobile App Architecture and Functionalities

To address transparency regarding the technical and functional design of the E-Walk app, a dedicated description of the app’s planned architecture is provided below. While the app is still under development, the design roadmap and anticipated features are outlined to ensure clarity and reproducibility. The E-Walk application will be developed as a cross-platform native app using interface development technologies that ensure compatibility with both Android and iOS devices. Data storage and backend functionalities will rely on a platform providing secure, cloud-based management of activity metrics, user profiles, and educational content. This architecture enables real-time data synchronization, offline use, and scalable data handling. The key functionalities will be as follows:Physical activity tracking: Integration of GPS tracking and step counters to record activity duration, distance, and intensity. Data will be complemented by user-reported activity logs.Educational modules: short interactive quizzes and mini-games designed to stimulate cognitive engagement, aligned with topics identified through concept mapping.User interaction modes: options for individual challenges and team-based competitions, allowing flexible engagement and promoting social motivation.Feedback collection: in-app surveys, ratings, and motivational prompts to capture user enjoyment, preferences, and suggestions.Gamification elements: points, badges, and leaderboards to reinforce engagement and reward consistent participation.

All collected data will be anonymized and securely stored on the Firebase platform, with strict adherence to data protection regulations. Parents and teachers will have access to summarized reports of physical activity and educational engagement.

The app will follow an iterative development process:Prototype phase: initial interface and feature mockups tested with a small sample of children and teachers.Pilot testing: functional beta version deployed to evaluate usability, data collection accuracy, and engagement.Full deployment: iterative refinement based on pilot feedback, including scaling educational content and activity tracking features.

This structured design ensures that the E-Walk mobile application will be robust, user-friendly, and aligned with the needs and expectations of primary school students.

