In line with the study’s objectives, specific success indicators will be used to evaluate the impact of the intervention. Primary indicators will include changes in physical activity metrics such as daily step count, minutes of moderate-to-vigorous activity, and reductions in sedentary time, as recorded through app-based measures and validated questionnaires. Physical activity levels will be assessed using the Physical Activity Questionnaire for Older Children (PAQ-C) [31] for children (students aged 9–15 years) and the short version of the International Physical Activity Questionnaire (IPAQ) [32] for teachers (adults aged ≥ 18 years old). The PAQ-C is a self-administered tool for children, providing a score from 1 (low activity) to 5 (high activity) based on nine items. The tenth item, related to illness, is not included in the final score. The PAQ-C has been validated in different countries and cultural contexts, demonstrating good reliability for assessing self-reported physical activity among school-aged children [31]. It has been translated into multiple languages and adapted to local habits (e.g., types of common sports or leisure-time activities), which makes it suitable for use in our multinational study context. The IPAQ includes 7 items assessing frequency, intensity, and duration of physical activity, along with sitting time. It includes both categorical (inactive, minimally active, HEPA active) and continuous scores (MET-minutes/week) [33,34]. The IPAQ has been validated for adults in more than 20 countries, with standardized translations and cultural adaptations [32]. In addition, anthropometric parameters will be collected as complementary success indicators to monitor changes in body composition and overall health status during the project. Weight and height will be determined using a precision instrument that combines a scale and stadiometer accurate to 0.1 kg and 0.1 cm (Seca, model 709, Vogel & Halke, Hamburg, Germany). Additionally, the BMI will be calculated. Both physical activity levels and anthropometric data will be evaluated for the entire three-year duration of the project.

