### 2.6. Statistical Analysis

The evaluation phase of the project will adopt a quasi-experimental pre-post design without randomization. Children and schools will first participate in the baseline assessment (anthropometric data, PAQ-C/IPAQ, app usage, and engagement metrics), followed by the implementation of the mobile app and sport activities. Post-intervention assessments will be conducted at multiple time points (e.g., 6 months and 12 months after implementation) to examine changes in physical activity levels, sedentary behaviors, and anthropometric outcomes relative to baseline. The statistical methods and analyses that will be applied to investigate the effect of the mobile app, specifically designed based on a concept mapping approach, on physical activity engagement and educational interaction in primary school students are specifically detailed in Supplementary File S1 [35,36].

All analyses will be performed using STATA 18 (StataCorp LP, College Station, TX, USA).

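### Refinement of activity tracking is listed under full deployment with no end point, although the app records some of the primary indicators, so a software change between waves could pass for a change in activity

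*Protocol article*

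**What the plan says.** Section 2.5.2 sets out three development stages: a prototype, a pilot with a beta version, and full deployment. The accuracy of data collection is listed as something the pilot evaluates. The third stage, full deployment, is described as "iterative refinement based on pilot feedback, including scaling educational content and activity tracking features". No date or milestone closes this refinement.

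Section 2.5 states that "Primary indicators will include changes in physical activity metrics such as daily step count", together with moderate-to-vigorous activity minutes and sedentary time, "as recorded through app-based measures and validated questionnaires". Section 2.5.2 gives the app's part in this: "Integration of GPS tracking and step counters to record activity duration, distance, and intensity", complemented by logs that users fill in themselves. The children's questionnaire, PAQ-C, is described in Section 2.5 as "providing a score from 1 (low activity) to 5 (high activity) based on nine items". IPAQ, used for the teachers, yields MET-minutes per week and sitting time.

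Section 2.6 plans a non-randomised pre-post evaluation with follow-up at "multiple time points (e.g., 6 months and 12 months after implementation"), each compared with baseline. No concurrent control group is described. Section 2.5 has activity levels evaluated over all three years of the project.

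**The concern.** The app is both the intervention and one of the measuring instruments. A measuring instrument should stay the same over the period in which change is estimated. The only accuracy check described comes in the pilot, and the stage after it still allows tracking to be refined.

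Without a concurrent control group, a change in how steps, intensity or inactive time are recorded coincides with the passage of time, which is also the contrast of interest. An apparent gain or loss in steps could then be partly or wholly a software effect. Section 5 offers objective indicators, app-based engagement metrics among them, as a complement to self-report, which it concedes is open to recall error and social desirability bias. Falling back on the questionnaires alone would weaken that safeguard.

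**Working it through.** The documents give no sample size, standard deviation or expected effect to reproduce, and the point needs none. The check has four steps.

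**1. Which outcomes depend on the app.**

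| Indicator (Section 2.5) | Children: sources described | Teachers: sources described |
|---|---|---|
| Daily steps | app only | app only |
| Activity minutes | app and its user-reported logs; PAQ-C gives a 1 to 5 score, not minutes | app and logs; IPAQ |
| Sedentary time | app-based measures; PAQ-C gives no minutes | app-based measures; IPAQ sitting time |

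The questionnaires do not move with a software update. Children's step counts have no second source.

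**2. How a recording shift enters the estimate.** Let T be the true mean change between two app-based measurements, and let b1 and b2 be the mean recording errors at the earlier and later one. Then

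observed mean change = T + (b2 − b1).

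If tracking is unchanged and behaves alike at both times, b2 − b1 is zero and the error cancels. If tracking changes in between, b2 − b1 passes into the estimate in full. It does not contain the sample size, so more children only narrow the interval around the shifted value.

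The app is to run on Android and iOS, and the shift may differ between them. With a share p of records on Android,

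net shift = p × (Android shift) + (1 − p) × (iOS shift).

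The mean change stays unbiased only if this sum is zero.

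**3. Size.** Both inputs below are assumptions: a recorded mean of 8,000 steps/day and a net shift of 2 to 10%, with no true change (T = 0).

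- 0.02 × 8,000 = 160 steps/day
- 0.05 × 8,000 = 400 steps/day
- 0.10 × 8,000 = 800 steps/day

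These figures show what a given shift would do. They do not show that a shift of that size is likely.

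**4. Which comparisons are exposed.** Section 2.6 lists the baseline assessment as anthropometry, PAQ-C/IPAQ, app usage and engagement metrics, and places the app's implementation after it. App-recorded steps are not named at baseline. If steps are first recorded after implementation, the exposed comparisons are those between later app-based measurements, for example an early one against 6 months, or 6 against 12 months. If the app also records steps at baseline, the change from baseline is exposed too. The identity in step 2 is the same in either case.

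**The case against.** The strongest reply concerns timing. The refinement is tied to pilot feedback, and other sections put development first. Section 2.5 has students use the app once it is developed, and the Discussion has it developed and then evaluated. On that reading, pilot lessons are built into the released version and nothing changes between waves. This stands as a plausible reading, but the text does not secure it: the refinement is called iterative, sits under full deployment and has no end point.

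Three stronger conclusions are tempting, and the documents do not support them.

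- **That the plan commits to changing the algorithm between waves.** The wording speaks of scaling tracking features, which may mean extending them. It does not say that the derivation of steps or intensity will change, although an added feature can also alter what is recorded.
- **That the app is the sole source of the primary indicators.** PAQ-C and IPAQ contribute too. A rise in steps with a flat PAQ-C score would be a warning, though it could not separate the two explanations.
- **That every child would shift in the same direction.** Nothing says an update acts alike on both operating systems or on all devices. Only the net shift matters for the mean.

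It may also be said that version logging is operational detail, and that the statistical methods are in Supplementary File S1, which is not shown. That is fair as to missing detail. The point rests instead on a development rule that Section 2.5.2 does state, and an analysis cannot undo an instrument change if neither versions nor raw counts were kept.

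**Conclusion.** The point holds as a risk that the wording leaves open. Followed as written, Section 2.5.2 allows the tracking component to change while outcome data are being collected. Sections 2.5 and 2.6 then give no way to separate a resulting recording shift from a real change in app-recorded activity.

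The conclusion rests on three conditions: tracking is altered between app-based measurements used in the analysis, the shifts do not cancel across platforms, and there is no concurrent control group, as in the text shown. The size is unknown; 160 to 800 steps/day follows only from the assumed 2 to 10% and 8,000 steps/day. Questionnaire and anthropometric outcomes are not affected. It does not invalidate the evaluation, but it should be settled before data collection because unlogged versions and discarded raw counts cannot be recovered.

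**What to change.** Reword the full-deployment item in Section 2.5.2 and align Sections 2.5 and 2.6 with it:

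- Pilot-based refinement of tracking is completed, and the derivation of steps, intensity and sedentary time is frozen, before the first app-based measurement used in the analysis. The freeze lasts until the last follow-up wave.
- Refinement after that point is limited to educational content and interface.
- App version and operating system are stored with each record, and raw counts are kept where available. If an update is forced, the waves can then be reprocessed with one derivation or analysed by version.
- Section 2.6 states whether app-recorded activity is measured at baseline, so that the start of the freeze is clear.

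The cost is protocol wording and a version-control rule. The downside is small: improvements to tracking wait until follow-up ends. Participatory work on content can continue.

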### 2.6. Statistical Analysis

The evaluation phase of the project will adopt a quasi-experimental pre-post design without randomization. Children and schools will first participate in the baseline assessment (anthropometric data, PAQ-C/IPAQ, app usage, and engagement metrics), followed by the implementation of the mobile app and sport activities. Post-intervention assessments will be conducted at multiple time points (e.g., 6 months and 12 months after implementation) to examine changes in physical activity levels, sedentary behaviors, and anthropometric outcomes relative to baseline. The statistical methods and analyses that will be applied to investigate the effect of the mobile app, specifically designed based on a concept mapping approach, on physical activity engagement and educational interaction in primary school students are specifically detailed in Supplementary File S1 [35,36].

All analyses will be performed using STATA 18 (StataCorp LP, College Station, TX, USA).

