### 2.3. Project Design and Implementation

Institutions interested in participating in the project’s activities will be involved. The E-Walk project will be carried out in several sequential phases, aimed at identifying the key features/factors/characteristics influencing children’s engagement in physical activity through the use of a mobile application. Data collection will occur in two main phases. In Phase 1 (Section 2.4), group concept mapping will be used to identify key features and inform the design of the app and its in-app challenges. Phase 2 (Section 2.5) will assess the impact of the deployed app and challenges, with data collected at baseline and follow-up. Baseline measures will include questionnaires and anthropometric data, process measures will track app usage and challenge completion, and outcome measures will assess changes in physical activity, sedentary behavior, and BMI.

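### Section 2.6 lists app data at a baseline that precedes the app, and no described instrument gives children a pre-app value for steps, MVPA minutes or sedentary time

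*Protocol article*

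**What the plan says.** Section 2.6 (Statistical Analysis) sets the evaluation out as a non-randomised pre-post study. Children and schools first have a "baseline assessment (anthropometric data, PAQ-C/IPAQ, app usage, and engagement metrics), followed by the implementation of the mobile app". Follow-up comes at several times, with 6 and 12 months after implementation as examples, and outcomes are compared with baseline.

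Section 2.3 (Project Design and Implementation) sorts the measures differently: "Baseline measures will include questionnaires and anthropometric data, process measures will track app usage and challenge completion".

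Section 2.5 (Phase 2: Evaluation) names the endpoints: "Primary indicators will include changes in physical activity metrics such as daily step count, minutes of moderate-to-vigorous activity, and reductions in sedentary time". It gives two sources for them, the app and questionnaires. In the same section, children complete the PAQ-C, described as "providing a score from 1 (low activity) to 5 (high activity) based on nine items". Teachers complete the short IPAQ, described as covering how often, how hard and how long people are active, and also sitting time.

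Section 2.5.2 lists the tracking function of the app: "Integration of GPS tracking and step counters to record activity duration, distance, and intensity", supplemented by activity logs that users enter. No separate pedometer or accelerometer is named anywhere in the article.

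**The concern.** A pre-post study without a comparison group has one comparator, the value before the intervention. Section 2.6 appears to supply app data at that point, but its own sequence makes this impossible: the assessment comes first and the app follows. If the app entries are struck out, as section 2.3 implies they should be, nothing is left at baseline that measures the named primary indicators in children.

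A team that follows the stated sequence would reach follow-up with app-recorded steps and activity minutes and no earlier value to subtract. After deployment, an untreated reading from the app can no longer be collected prospectively. The early weeks of app use would not be a clean replacement, because section 2.5.2 puts the tracking in the same app as the points, badges, leaderboards, challenges and motivational prompts.

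There is a further cost. Section 5 (Limitations) accepts that PAQ-C and IPAQ are open to recall and social-desirability bias, and offers anthropometric and app-based data as objective complements. App data without a pre value cannot corroborate a self-reported change in activity.

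**Working it through.** No arithmetic applies. The article states no effect size or sample size that bears on this point, and the question is whether a measurement exists. The check traces each indicator to an instrument, a respondent group and a time.

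**Step 1: order of events.** Section 2.6 puts baseline before implementation. Section 2.3 places both baseline and follow-up in Phase 2, after the app has been designed in Phase 1. At baseline, therefore, the app has been designed but is not yet in use by participants.

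**Step 2: source of each indicator before the app is implemented.**

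- *Daily steps.* The only counter described is the app's (2.5.2). Children: no pre-app value. Teachers: no pre-app value.
- *MVPA minutes.* The app records duration and intensity (2.5.2), but only once in use. The PAQ-C is described as a 1-5 score, not as minutes (2.5). Children: no pre-app value. Teachers: available from IPAQ duration by intensity.
- *Sedentary time.* The PAQ-C is not described as measuring it. IPAQ sitting time is for teachers. Children: no pre-app value. Teachers: available.
- *PAQ-C score, IPAQ score, BMI.* All are collected at baseline in both 2.3 and 2.6. Change is computable.
- *App usage and engagement.* Listed at baseline in 2.6, but not observable until the app is implemented.

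**Step 3: count.** Of the three named primary indicators, 0 of 3 have a described pre-app source in children and 2 of 3 have one in teachers.

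**Step 4: can the user-entered logs fill the gap?** They are listed as part of the app's own tracking function, so they start when the app does.

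**Step 5: is there another comparator?** The article describes no control group and no randomisation. The contrast in 2.6 is change relative to baseline.

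**The case against.** Several points on the other side are sound, and they limit how far the finding goes.

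- A reader might infer that the app does not exist at baseline. The article does not say so. Phase 1 covers app design, and section 2.3 says "Phase 2 (Section 2.5) will assess the impact of the deployed app and challenges, with data collected at baseline and follow-up". Section 2.5.2 also plans a prototype and a beta pilot before full deployment. What is missing at baseline is the app in participants' hands.
- A reader might infer that no change from baseline can be computed at all. That is too broad. Section 2.5 names questionnaires alongside the app as sources. Teachers have IPAQ values for active time and sitting time, and PAQ-C and BMI changes can be analysed in children.
- A reader might take section 2.3 to restrict baseline to questionnaires and anthropometry. Its wording is inclusive, not exclusive. The conflict with 2.6 is that app usage is a process measure in one place and a baseline measure in the other.
- A reader might assume that the first week of app use will serve as baseline and try to put a size on the resulting bias. The article proposes no such analysis and gives no figure for early novelty, so any percentage would be guesswork.
- Section 2.5.1 leaves the exact app metrics to the concept-mapping results, and section 2.6 refers to Supplementary File S1, which is not shown. S1 might describe a run-in. However, it is cited for statistical methods, which cannot create a measurement that was not taken, and the sequence printed in 2.6 contains no run-in.
- Section 2.1 puts the main focus on design and development, and the Discussion calls effectiveness a secondary aim. The defect therefore leaves the concept-mapping phase untouched. It still affects what section 2.5 labels primary indicators of the evaluation.

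None of these supplies children with a pre-app value for steps, MVPA minutes or sedentary time.

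**Conclusion.** The point holds for children and for the three named indicators. Section 2.6 lists app usage and engagement at a baseline that comes before the app, section 2.3 classifies app usage differently, and the change-from-baseline primary indicators in section 2.5 have no described pre-app source in the target population. In an uncontrolled pre-post design, that leaves those changes without a valid comparator as written.

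The size is a count, not a bias estimate: none of the three indicators is covered in children. In teachers only daily steps are uncovered. PAQ-C, IPAQ and BMI are unaffected.

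This rests on two assumptions: that the instruments deliver what the article says they deliver, and that the sequence in section 2.6 is the one to be followed. A pre-app measurement specified in the supplement would remove the gap in the indicators, but the wording of 2.3 and 2.6 would still need to be reconciled.

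**What to change.** First, reconcile sections 2.3, 2.5 and 2.6 by deleting app usage and engagement metrics from the baseline list in 2.6. Then take one of two routes.

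(a) **Create a pre-intervention value.** Release the app first in a measurement-only mode for a short period fixed in advance, with sensors on and no feedback, points or challenges. Use that period as the baseline and then unlock the intervention. Alternatively, with consent, import the phone's step history from before installation; this serves the step baseline only. The run-in covers sedentary time only if the app records it, which the tracking list in 2.5.2 does not mention, so this should be stated. The cost is a feature lock and a short delay. The article says the app is still under development, so the lock can be built in now.

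(b) **Narrow the claims.** Reclassify app-recorded metrics as post-deployment process measures. Restrict change-from-baseline claims to PAQ-C in children, IPAQ in teachers, and BMI. State that a change in children's sedentary time cannot be claimed, because no described instrument gives it a baseline, and bring the statements on sedentary time in 2.5, 2.6 and the Conclusions into line. The cost is wording, plus giving up the children's step, MVPA-minute and sedentary-time changes as primary indicators.

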## 2. Materials and Methods

### 2.1. Ethical Approval and Experimental Approach to the Problem

The E-Walk project obtained ethical approval from the Institutional Review Board of the Department of Human Sciences, Society and Health at the University of Cassino and Lazio Meridionale (Approval No.: 19764, dated 16 July 2025). To establish a comprehensive European framework of physical inactivity among children aged 9 to 15 years, the project will adopt an ethnographic approach integrated with concept mapping. This design will allow the exploration of children’s relationships with mobile apps, together with the perceptions of both students and teachers from diverse countries and contexts. By combining real-world insights with scientific expertise, this study aligns with an obligation–opportunity conceptual model.

Given the relatively broad age range (9 to 15 years), potential differences in motivations, developmental stages, and physical activity behaviors will be acknowledged and accounted for in the analyses by including age as a covariate or stratifying results by age group. The study primarily focuses on the design and development stages through group concept mapping, with the subsequent evaluation phase planned as a quasi-experimental pre-post study to assess the app’s impact on physical activity and sedentary behaviors.

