### 2.2. Participants and Inclusion/Exclusion Criteria

Participants will include primary school students aged 9 to 15, schoolteachers, physical activity stakeholders, and relatives or guardians. Students will be subsequently divided into two age groups (9 to 12 and 13 to 15). Inclusion will be restricted to those regularly enrolled in primary schools and able to read and understand the language of the validated questionnaires used in each country. Only children with access to a compatible mobile device, either personal or shared, will be admitted. Those with medical conditions or physical disabilities that contraindicate moderate-to-vigorous physical activity, or with cognitive or developmental impairments that prevent them from comprehending the app content or questionnaire items, will not be eligible.

Teachers will be eligible if employed at one of the participating schools or directly involved in school activities. They must be able to complete the questionnaires and engage with app-related tasks, possessing sufficient digital literacy to use a smartphone or tablet. Adults with severe health conditions preventing participation in physical activity or those unable to engage with digital tools will be excluded.

Parents, guardians, and other stakeholders will be included if directly involved in supporting children’s education or physical activity and available to participate in focus groups, surveys, or feedback activities related to the intervention. Those lacking sufficient access to digital devices and literacy to engage with the app-based activities will be excluded.

Recruitment will take place through workshops organized in one or more local schools, ensuring a diverse range of ages and socio-cultural backgrounds. Participation will be voluntary, and all participants will be fully informed about the project and its aims. They will be allowed to withdraw from the study at any time without consequences. Written informed consent will be obtained from the participants. For children, written parental consent will also be required. In accordance with Regulation (EU) 2016/679 of the European Parliament and Council on the protection of personal data (General Data Protection Regulation), each participant will be assigned an anonymous identification code. All collected data will be used exclusively for statistical and research purposes.

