## 4. Conclusions

This protocol outlines the rationale and methodological framework of the E-Walk project, which integrates group concept mapping with the development of a mobile app to promote physical activity and reduce sedentary behaviors. By engaging key stakeholders, children, teachers, families, and physical activity professionals, the project aims to ensure that the app is user-centered, contextually relevant, and sustainable. The evaluation phase, based on predefined success indicators, will generate evidence on the app’s effectiveness in improving physical activity levels, reducing sedentary time, and supporting healthier growth trajectories. The E-Walk intervention has the potential to contribute to school-based health promotion strategies, strengthen the integration of digital tools in education, and advance public health goals related to child well-being.

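### Change from baseline with no comparison group is to be reported as the app's effectiveness, while ageing, growth and possibly season stay in the estimate and are not named as limitations

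*Protocol article*

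**What the plan says.** All references are to the protocol article.

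- **Design (2.6, also 2.1).** "The evaluation phase of the project will adopt a quasi-experimental pre-post design without randomization". No control, waiting-list or staggered-start group is mentioned anywhere.
- **Contrast (2.6).** The later assessments serve "to examine changes in physical activity levels, sedentary behaviors, and anthropometric outcomes relative to baseline".
- **Timing (2.6).** "Post-intervention assessments will be conducted at multiple time points (e.g., 6 months and 12 months after implementation"). The times are examples, they run from implementation, and the calendar month of baseline is not given.
- **Age (2.1, 2.2).** Differences across the 9 to 15 range are to be handled by "including age as a covariate or stratifying results by age group". Section 2.2 sets the groups: "Students will be subsequently divided into two age groups (9 to 12 and 13 to 15"). Section 2.1 does not say whether the covariate is age at baseline or age at each assessment.
- **Intended reading (section 4).** The evaluation "will generate evidence on the app’s effectiveness in improving physical activity levels, reducing sedentary time, and supporting healthier growth trajectories". The abstract also speaks of effectiveness. The closing summary of section 3 is softer and speaks only of potential effectiveness.
- **Limitations (section 5).** Self-report, selection, age heterogeneity, the digital divide, school resources and motivation are listed. The absence of a comparator, maturation and season are not.

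**The concern.** In an uncontrolled pre-post study, the mean change is the app effect plus everything else that moves the outcome over the same interval. Children aged 9 to 15 grow and mature over 6 to 12 months whether or not they use an app. BMI is an outcome (2.3, 2.5), so a claim about healthier growth is the most exposed. The intervention is walking, running, hiking or rolling along routes (2.5), and step count is a primary indicator, so weather and daylight could also matter.

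The only adjustment the article names is for age, and it is introduced to deal with differences between children. If the article is followed as written, background change would be credited to the app, or a real benefit would be masked by it. Readers of section 5 would not be warned of either.

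**Working it through.** The article gives no sample size, SD, alpha or power, so there is no figure of its own to reproduce. The check is algebra, a simulation and an illustrative error rate. Every numerical input below is an assumption, not a figure from the article.

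**1. What the contrast estimates.** At *t* years after baseline, with no comparison group:

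expected change = app effect + *b·t* + *A*[cos 2π(*t*+φ) − cos 2πφ]

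Here *b* is within-child ageing per year, *A* the seasonal half-amplitude and φ the point in the seasonal cycle at baseline.

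**2. Ageing.** Assumed *b* = −0.10 PAQ-C points per year, no season, app effect zero. Algebra gives −0.05 at 6 months and −0.10 at 12 months. The simulation used 4,000 children aged 9 to 15 with a residual SD of 0.4, so its error on a change is about 0.4×√2/√4000 = 0.009.

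| Analysis | 6 months | 12 months |
|---|---|---|
| Unadjusted | −0.049 | −0.096 |
| Baseline age as covariate | −0.049 | −0.096 |
| Stratum 9–12 | −0.045 | −0.095 |
| Stratum 13–15 | −0.054 | −0.098 |
| Age at assessment, cross-sectional slope −0.10 | −0.002 | −0.003 |
| Age at assessment, cross-sectional slope −0.05 | −0.033 | −0.041 |
| Age at assessment, cross-sectional slope 0 | −0.047 | −0.107 |

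Baseline age is constant within a child, so it cannot alter a within-child change. The same holds for strata. Age at assessment leaves a bias of (within-child slope − cross-sectional slope)×*t*. That is zero if the two slopes agree, −0.025 and −0.05 if the cross-sectional slope is half as steep, and −0.05 and −0.10 if it is flat. The simulation agrees within its error.

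**3. Season.** Assumed *A* = 0.15, no ageing, app effect zero, and a full six months between baseline and the first follow-up.

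| Baseline position | 6 months, formula | 6 months, simulated | 12 months, simulated |
|---|---|---|---|
| Trough | 0.15×[1 − (−1)] = +0.30 | +0.288 | −0.017 |
| Peak | 0.15×[−1 − 1] = −0.30 | −0.301 | +0.010 |
| Midway | 0 | +0.002 | +0.007 |

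Adjusting for baseline age leaves these values unchanged. Age at assessment moves them by at most 0.004, within simulation error. Season therefore bears on the 6-month contrast and cancels at 12 months, whereas ageing affects both and is larger at 12 months.

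**4. How often a background shift would be significant.** Paired t-test, two-sided 5%, app effect zero, assumed PAQ-C SD 0.7, within-child correlation *r* of 0.5 or 0.7.

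SD of change = 0.7×√(2(1−*r*)) = 0.70 (*r* = 0.5) or 0.54 (*r* = 0.7). Non-centrality = shift ÷ (SD of change/√*n*). For a shift of 0.1 and *n* = 200 this is 0.1/0.0495 = 2.02 or 0.1/0.0383 = 2.61. The noncentral t distribution then gives:

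| Shift | *n* = 60 | *n* = 100 | *n* = 200 | *n* = 400 |
|---|---|---|---|---|
| 0.05 | 9–11% | 11–15% | 17–25% | 30–45% |
| 0.10 | 19–29% | 29–45% | 52–74% | 81–96% |
| 0.20 | 59–80% | 81–96% | 98–100% | about 100% |

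The nominal rate is 5%. The excess grows with *n*, so a larger study does not cure it. The calculation treats children as independent and ignores clustering in schools.

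**The case against.** The article discloses the design twice as quasi-experimental pre-post. It says the study focuses mainly on design and development, treats the evaluation as a secondary aim, and in section 3 speaks only of potential effectiveness. The statistical methods are sent to Supplementary File S1, which is not shown and might contain season terms or standardised BMI. All of this is fair and limits how severe the point is. No analysis file can supply a missing comparator, however, and none can change the unqualified claims in the abstract and section 4 or the gap in section 5.

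Four stronger readings are tempting, and the documents do not support them:

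- **That the age adjustment cannot remove maturation.** This is exact for baseline age and for the two strata. Section 2.1 says only age, and age at assessment could remove maturation if cross-sectional and within-child trends agree.
- **That 6 months puts follow-up in the opposite season and biases the result in a known direction.** The times are examples counted from implementation, the gap from baseline to implementation is unstated, and so is the baseline month. A baseline midway between peak and trough gives almost no seasonal bias.
- **That the schedule contradicts itself.** Section 2.5 says "Both physical activity levels and anthropometric data will be evaluated for the entire three-year duration of the project". Visits at 6 and 12 months, and any later ones, can fit inside three years, so there is no conflict.
- **That the error rates measure the bias in this study.** They rest on assumed SD, correlation, shift and sample size, and show only that a small background shift is easily declared significant.

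**Conclusion.** The point holds in this form. The design yields change from baseline with no comparator, while the abstract and section 4 promise effectiveness, including on growth, and section 5 leaves out the missing control, maturation and season. Baseline age or age strata leave the whole ageing component in the estimate. A seasonal difference at 6 months is possible, but its size and sign cannot be determined from the article.

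The structural conclusion needs no numerical assumption, but its size cannot be fixed from the article. Under the stated assumptions, a background shift of 0.1 PAQ-C points alone is significant in 52-74% of studies of 200 children and in 29-45% of studies of 100.

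**What to change.** 1. **Section 2.6, timing.** Make an assessment about 12 months after baseline, in the same calendar month as baseline, the main time point. Treat 6 months as descriptive. Count the interval from baseline, since the present examples run from implementation.
2. **Sensitivity analysis.** Use age at assessment and calendar month rather than baseline age alone. State that this removes maturation only if cross-sectional and within-child age trends agree. If they do not, some or all of the bias stays.
3. **Abstract and section 4.** Replace effectiveness with change after deployment, including for growth.
4. **Section 5.** Name the absence of a comparison group, maturation and season as limitations.

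The cost is wording, the choice of calendar month for a visit already foreseen, and a little extra modelling. No further participants are needed. The price is that the 6-month result no longer supports an effect claim and the overall conclusion is weaker. These changes do not replace a concurrent or staggered comparison: other events over the year, retesting and regression to the mean would remain, which is why the wording change is needed even if the first two are made.
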